### Sample Size

The sample size calculation for the number of resident participants is based on the primary outcome measure in the pilot study: the number of sit-to-stands that the resident is able to complete in 30 seconds. Based on our earlier pilot work, we observed residents' ability to maintain and in some instances increase the number of sit-to-stands that they could complete in 30 seconds. We judge an increase of two sit-to-stands completed in 30 seconds to be a meaningful change in the residents' mobility. Based on existing research [10,38,46,47] and the pilot study, the standard deviation of the 30-second sit-to-stand measure is 3.5 sit-to-stands. Thus we will need 49 residents in each of the intervention and the control groups to detect an increase in the number of sit-to-stands that the resident is able to complete in 30 seconds (power = 0.80; 2-tailed; α = 0.05). Assuming an attrition rate of 20% over 6 months we will recruit 60 residents to the intervention group and 60 residents to the control group. We expect to succeed in recruiting and following our sample of 120 residents based on our experience with the pilot study and the experience of [name] who recruited similar samples in two previous studies using similar recruitment methods [4,48].

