### Control group

Resident participants in the control facilities will receive usual care. The only change in their routine will be the measurement of mobility, function and health-related quality of life on three occasions as for residents in the intervention group. Health care aides may work in more than one unit in a facility thus intervention and control groups will be designated at the facility level rather than the unit level to avoid contamination of the control group. It is also possible that some health care aides may work in more than one facility. We will assess the extent of contamination of the control group at the end of the study by asking health care aides who work control facilities if they have ever encouraged residents in the control facilities to repeat sit-to-stands.

LTC facilities in the intervention group will be matched to the control group facilities on ownership model (public, private for-profit, voluntary not-for-profit) and size because quality of care and resident outcomes are associated with ownership models [49-54] and size [48,49,52]. To assess the comparability of the intervention and control facilities a research assistant will gather information about each facility by: a) interviewing managers to obtain information such as staff-to-resident ratios on each shift, availability of rehabilitation services and size of units; b) observing activity across both the day and evening shifts using a structured observation schedule; and c) measuring environments using two standardized instruments: the Alberta Context Tool and the Professional Environmental Assessment Protocol (PEAP). Drawing on data collected from the observations and data elicited during the manager interviews, total PEAP scores will be calculated immediately following each manager interview.

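### The stated 80% power treats residents as independently allocated, although three whole facilities form each arm, so on the plan's own inputs it is not the power of a valid 5% test under any positive intracluster correlation

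*Protocol article*

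**What the plan says.** The Sample Size section of the protocol article gives every input to its calculation:

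- Difference: "We judge an increase of two sit-to-stands completed in 30 seconds to be a meaningful change in the residents' mobility".
- Spread: "the standard deviation of the 30-second sit-to-stand measure is 3.5 sit-to-stands".
- Error rates: "power = 0.80; 2-tailed; α = 0.05".
- Result: "Thus we will need 49 residents in each of the intervention and the control groups to detect an increase".
- Only inflation: "Assuming an attrition rate of 20% over 6 months we will recruit 60 residents to the intervention group and 60 residents to the control group".

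The section mentions no ICC, design effect or number of facilities. The only ICC in the article is a reliability coefficient for the QOL-AD.

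The Abstract names three intervention and three control facilities. The Control group section says that "intervention and control groups will be designated at the facility level rather than the unit level to avoid contamination of the control group". The same section justifies matching on ownership and size by the association of both with quality of care and resident outcomes.

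The Data Analysis section plans a mixed between-within analysis of covariance. Group is the between-subjects factor, time is the within-subject factor, and facility characteristics are among the covariates.

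**The concern.** The unit of assignment is the facility, but the calculation counts residents as if each had been assigned separately. Residents of one facility share staff, routines and environment, and the article itself expects outcomes to differ between facilities. Any such shared variation enlarges the standard error of the group comparison beyond what the formula allows. Three facilities per arm also give very little information about how large that variation is.

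The stated 0.80 shapes how the result will be read. If the comparison respects the facilities, real power may be well below 80%, and a null result could be taken as better evidence of no effect than it is. If the comparison ignores the facilities, the hazard is the opposite one: the test rejects too often when there is no effect. In neither case is 0.80 the power of a 5% test of this design.

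**Working it through.** **1. Reproduce the plan's figure.** Inputs from the Sample Size section: difference 2, SD 3.5, two-sided alpha 0.05, power 0.80.

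n per group = 2 × (1.960 + 0.8416)² × 3.5² / 2² = 48.07, rounded up to 49.

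The two-sample t-test with 49 per group has power 0.7996. So 49 is exactly the independent-residents formula, with no room in it for a hidden design effect.

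**2. Expected completers.** 60 × (1 − 0.20) = 48 per arm, or 48 / 3 = 16 per facility if spread evenly. Being one short of 49 costs under one point of power (0.791 against 0.800) and does not drive what follows.

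**3. Add the facilities.** The article gives no ICC, so 0.01, 0.02 and 0.05 are assumptions.

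- Design effect: DE = 1 + (16 − 1) × ICC.
- Standard error of the group difference: SE = 3.5 × √(2 × DE / 48).
- Power: noncentral t with noncentrality 2 / SE, on 94 df (design effect only) or on 2 × 3 − 2 = 4 df (facility-level test).
- Detectable difference: the difference that gives 80% power with the same SE.

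| ICC | DE | SE | Power, 94 df | Power, 4 df | Detectable, 94 df | Detectable, 4 df |
|---|---|---|---|---|---|---|
| 0.01 | 1.15 | 0.766 | 73% | 51% | 2.2 | 2.9 |
| 0.02 | 1.30 | 0.815 | 68% | 46% | 2.3 | 3.1 |
| 0.05 | 1.75 | 0.945 | 55% | 37% | 2.7 | 3.6 |

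**4. If residents are analysed as independent.** The true type I error of the nominal 5% test is about 2 × [1 − Φ(1.96 / √DE)]:

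- ICC 0.01: 1.96 / √1.15 = 1.83, about 7%.
- ICC 0.02: 1.96 / √1.30 = 1.72, about 9%.
- ICC 0.05: 1.96 / √1.75 = 1.48, about 14%.

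**5. What baseline adjustment could recover.** Replace 3.5 by 3.5 × √(1 − r²), where r is the correlation between baseline and follow-up. The article gives no r, so 0.7 and 0.8 are assumptions, as is leaving the ICC unchanged by the adjustment. The SD becomes 2.50 at r = 0.7 and 2.10 at r = 0.8. Power with 48 per arm on 4 df:

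| ICC | r = 0.7 | r = 0.8 |
|---|---|---|
| 0.01 | 78% | 89% |
| 0.02 | 73% | 86% |
| 0.05 | 61% | 75% |

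**The case against.** **The planned analysis may still have 80% power.** Outcomes are measured at baseline, 3 and 6 months, and a repeated-measures analysis of covariance is planned, whereas the calculation uses the unadjusted SD. With r = 0.8, power exceeds 80% at ICC 0.01 and 0.02 even on 4 df. With r = 0.7 and no df penalty, it is about 95% at ICC 0.01 and 83% at 0.05. This objection stands as far as it goes. A reader might infer that the design cannot deliver 80% power, and the document does not support that. But the sample-size section neither uses this gain nor gives a correlation, so the gain cannot justify the figure as written.

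**The facility-level test on 4 df is not stated in the plan.** This is correct. It is tempting to say that power is only 56% even at ICC 0, but that drop comes entirely from imposing a 4-df test. A resident-level test would be valid at ICC 0 and would have about 79% power with 48 per arm. That is why the design effect and the df penalty are shown separately above.

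**The arithmetic is right.** It is, for its formula. The fault is that the formula does not match the assignment.

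**Matching and facility covariates address facility differences.** They may lower the residual ICC. With six facilities they cannot restore degrees of freedom, and the calculation makes no reference to them.

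**An analysis plan may deal with clustering.** It may, and the lack of analysis detail is not the point here. A later plan cannot make 49 residents give 0.80 on the inputs stated here once the ICC is above zero.

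**Conclusion.** The point holds as a mismatch between the calculation and the design. The 0.80 with 49 per group belongs to a trial that assigns residents independently, and this trial assigns three facilities to each arm. On the plan's own difference and SD, any positive ICC means that the stated power is not that of a valid 5% test. That direction does not depend on the ICC chosen.

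The size does depend on it, and the ICC values are assumptions. At ICC 0.01 to 0.05, unadjusted power is about 73% to 55% from the design effect alone, and 51% to 37% on 4 df.

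It is not established that the adjusted analysis falls below 80%. That turns on a correlation and an ICC that the article does not give. The shortfall of one completer per arm is real but trivial, and it does not carry the conclusion.

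**What to change.** Keep the 120 residents and rewrite the Sample Size section so that it:

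- states an assumed ICC range with its basis, and the design effect at 16 completers per facility;
- states the degrees of freedom that six facilities leave;
- gives the resulting power for a difference of 2 and the difference detectable with 80% power, as in the table in the working;
- gives the power of the baseline-adjusted analysis over a stated range of correlations, since that is where much or all of the loss may be recovered;
- states that 48 completers per arm are expected after 20% attrition.

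The change is to text only. It adds no residents and no measurements. Its cost is a stated power that is less favourable, and more dependent on stated assumptions, than the present 0.80.

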### Procedure

As the first residents are recruited from each intervention facility we will introduce the sit-to-stand intervention to the intervention facilities on the units where the residents reside. A nurse educator contracted for the study will deliver 20 minute education sessions on the sit-to-stand functional activity to as many health care aides as possible who are working on both day and evening shifts. These 20 minute sessions will be offered between 8 and 32 times depending on the size of the intervention facility. During these small group education sessions we will: a) describe the potential rationale for the sit-to-stand activity; b) provide standardized instruction and practice of the activity; and, c) illustrate how to document resident participation with the sit-to-stand activity. Following the education sessions health care aides will begin to facilitate the sit-to-stand activity with residents in their care who have been recruited to the study. Our pilot study demonstrated that health care aides require encouragement at regular intervals to consistently integrate the sit-to-stand activity into their daily routine. Thus we have included knowledge translation interventions that were tested in the pilot study to optimize the likelihood that residents in the treatment group will perform the sit-to-stand activity. In the first month the nurse educator will return to the intervention facilities to converse with the health care aides about their experiences with the sit-to-stand activity and to facilitate problem-solving around any barriers that they may have encountered. In the second month a set of reminders will be introduced including: a) prominently posting the names of resident participants where the change of shift occurs; b) affixing a colourful sticker to residents' bedroom doors and beside their beds; and, c) marking with a sticker the usual documentation flowsheets where the health care aides record residents' shift-to-shift responses to the exercise. During the third month 20 minute problem solving sessions with health care aides will be conducted to identify barriers to completing the sit-to-stand activity and to suggest ways to overcome them. The next month a poster and small handouts that summarize the discussion and problem-solving sessions will be posted on the treatment units and distributed to the health care aides. Each month a different approach will be taken to heighten the awareness of the health care aides about the importance of continuing to integrate the sit-to-stand activity into the residents' activities of daily living.

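### The stated power of 0.80 holds only for independent residents analysed at resident level, but treatment is assigned to six whole facilities, so the stated power and the 5% level cannot both hold

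*Protocol article*

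**What the plan says.** The Sample Size section of the protocol article bases the trial on the 30-second sit-to-stand count. The target is a difference of two ("We judge an increase of two sit-to-stands completed in 30 seconds to be a meaningful change in the residents' mobility"), and "the standard deviation of the 30-second sit-to-stand measure is 3.5 sit-to-stands". With "power = 0.80; 2-tailed; α = 0.05", it concludes that "we will need 49 residents in each of the intervention and the control groups to detect an increase". It then allows for loss to follow-up: "Assuming an attrition rate of 20% over 6 months", "we will recruit 60 residents to the intervention group and 60 residents to the control group". The section mentions no facilities, ICC or design effect.

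The Control group section says that "intervention and control groups will be designated at the facility level rather than the unit level". The abstract gives three intervention and three control facilities, and Sampling and recruitment gives six in total. The Control group section matches facilities on ownership and size because outcomes vary with both. Covariates names the care environment as a predictor of mobility loss.

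Data Analysis describes a between-within analysis of covariance at resident level, with group as the between-subjects factor. Facility size, unit size, ownership and two environment scores (PEAP and ACT) are listed as covariates. No facility term is named.

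**The concern.** Residents of one facility share staff, routines and surroundings, so their outcomes tend to be correlated. When whole facilities are assigned, that correlation inflates the variance of the group difference, and with three facilities per group there is little information from which to estimate the inflation. A sample size that counts residents as independent takes account of neither.

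The consequence depends on the analysis. If facilities are respected, power for the two-stand difference is below the stated 0.80, and a non-significant result is weak evidence against benefit. If residents are treated as independent, the test rejects too often when there is no effect. Knowledge Translation says that decisions on practice or policy will draw on the findings, so both errors matter.

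**Working it through.** **Inputs.** From Sample Size: difference 2, SD 3.5, two-sided α 0.05, 49 analysed per group. From the abstract and Control group: 3 facilities per group. Assumed: equal facility sizes, m = 49/3 = 16.33, and ICC of 0.01, 0.02, 0.05 and 0.10, because the article gives none.

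**Reproducing the plan's figure.** n = 2 × SD² × (1.960 + 0.842)² / difference² = 2 × 12.25 × 7.849 / 4 = 48.07, rounded up to 49. At 49 per group, a t-test on independent residents has power 0.7996 (0.807 by the normal approximation). The figure therefore leaves no room for clustering. The attrition allowance adds none: 60 × 0.8 = 48 completers, t-test power 0.791.

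**Allowing for facilities.** Design effect DE = 1 + (m − 1) × ICC. Standard error SE = 3.5 × √(2 × DE / 49). Ratio λ = 2 / SE.

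- Power, design effect only: Φ(λ − 1.96).
- Power, facility-level test: noncentral t with noncentrality λ and 6 − 2 = 4 df (critical value 2.776).
- Detectable difference at 80% power on 4 df: 3.761 × SE, where 3.761 is the noncentrality that gives 80%.

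Example at ICC 0.05: DE = 1 + 15.33 × 0.05 = 1.767; SE = 3.5 × √(2 × 1.767 / 49) = 0.940; λ = 2.128; Φ(0.168) = 0.567.

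| ICC | DE | Power, DE only | Power, 4 df | Detectable difference, 4 df |
|---|---|---|---|---|
| 0 | 1.000 | 0.807 | 0.572 | 2.7 |
| 0.01 | 1.153 | 0.750 | 0.516 | 2.9 |
| 0.02 | 1.307 | 0.697 | 0.470 | 3.0 |
| 0.05 | 1.767 | 0.567 | 0.371 | 3.5 |
| 0.10 | 2.533 | 0.427 | 0.278 | 4.2 |

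**With baseline adjustment.** Assume a baseline correlation of 0.7 and the same ICC after adjustment. The SD becomes 3.5 × √(1 − 0.49) = 2.5.

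| ICC | Power, DE only | Power, 4 df |
|---|---|---|
| 0.01 | 0.958 | 0.785 |
| 0.02 | 0.934 | 0.737 |
| 0.05 | 0.846 | 0.614 |
| 0.10 | 0.701 | 0.474 |

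**Residents analysed as independent.** This uses SD 3.5, the normal approximation and no covariates. Type I error = 2 × [1 − Φ(1.96 / √DE)]. Probability of rejecting at a true difference of 2 = Φ((2.828 − 1.96) / √DE).

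| ICC | Type I error | Rejection at difference 2 |
|---|---|---|
| 0.01 | 0.068 | 0.791 |
| 0.02 | 0.086 | 0.776 |
| 0.05 | 0.140 | 0.743 |
| 0.10 | 0.218 | 0.707 |

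**The case against.** **The plan names no facility-level test.** This stands. Data Analysis describes a resident-level model, under which the chance of detecting a two-stand effect stays between 0.79 and 0.71. A reader might infer that the trial is simply underpowered and that a null result will be over-read. The article does not support that as the whole story: it does not say how a non-significant result will be interpreted, and under the analysis as written the larger problem is false positives.

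**Baseline and repeated measurements may recover power.** This stands in part. Outcomes are taken at baseline, 3 and 6 months. With an assumed correlation of 0.7, design-effect-only power exceeds 0.80 at ICC up to 0.05. On 4 df it stays below 0.80 at every ICC shown from 0.01 upwards. The correlation is not in the article, and Sample Size does not invoke the gain.

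**Matching and facility covariates reduce facility variation.** They may, so the residual ICC could be lower than the raw one. They do not replace a facility term. Six facilities leave 6 − 2 = 4 between-facility degrees of freedom after group. Facility size (1), three ownership models (2), PEAP (1) and ACT (1, as a single score) would need 5 if measured per facility.

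**Retention could be better than assumed.** With all 60 per group retained, power would be 0.82 (design effect only) or 0.58 (4 df) at ICC 0.01, and 0.61 or 0.40 at ICC 0.05.

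**A full protocol or analysis plan may handle clustering.** A cluster-aware model there would correct the type I error, but it would not make the published 0.80 true, because the section's own inputs give 49 only under independence.

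**Conclusion.** The point holds as one of design and power. The arithmetic in Sample Size is right for its inputs. What is wrong is the unstated assumption that residents are independent, in a design that assigns facilities.

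Without baseline adjustment, and for ICC from 0.01 to 0.10, power at a valid 5% level is 0.75 to 0.43 with the design effect only and 0.52 to 0.28 on 4 df. The second method gives only 0.57 at ICC 0, so it is not enough to say that 0.80 requires no facility effect: it also requires a resident-level analysis. If facilities are ignored, type I error is about 7%, 9%, 14% and 22% at the four ICC values, before covariates. Either way, power 0.80 and α 0.05 do not both hold.

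The sizes rest on an assumed ICC range and equal facility sizes. The 4 df figures should not be read as the trial's actual power, since no such test is planned and the ICC is unknown; they show what a facility-level test could deliver.

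**What to change.** Keep the 120 residents and amend the text as follows.

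- In Sample Size, state that 49 per group gives 0.80 only for independent residents analysed at resident level.
- Give power and detectable difference for three facilities per group over a stated ICC range (for example 0.01 to 0.10), with and without an assumed baseline correlation.
- State that the result, significant or not, will be interpreted through a confidence interval that accounts for facility, set against the two-stand difference.
- Report the observed ICC.

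The cost is a few sentences and a less favourable stated figure. No extra residents are needed.

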### Intervention

Health care aides will be trained to prompt residents to repeatedly stand up and sit down on four occasions during daily functional activities (twice on each of the day and evening shifts). The number of repetitions on each occasion will vary according to residents' ability and fatigue. The sit-to-stand activity is to be integrated into usual care routines such as when entering the dining room at mealtimes, while toileting, and on other occasions of regular activity. The timing and location will be at the discretion of the health care aide. Health care aides will be reminded that, as with their usual care activities, when a resident's condition deteriorates they should consult with the registered nurse or licensed practical nurse about the appropriateness of repeating the sit-to-stand activity.

### Intervention group

Residents in the three intervention facilities will be exposed daily to the intervention for 6 months. This will enable an assessment of the effect of the intervention on residents' mobility over time and a preliminary assessment of the sustainability of the intervention. Their mobility, function in basic activities of daily living, and health-related quality of life will be measured at baseline, 3 months and 6 months.

### Control group

Resident participants in the control facilities will receive usual care. The only change in their routine will be the measurement of mobility, function and health-related quality of life on three occasions as for residents in the intervention group. Health care aides may work in more than one unit in a facility thus intervention and control groups will be designated at the facility level rather than the unit level to avoid contamination of the control group. It is also possible that some health care aides may work in more than one facility. We will assess the extent of contamination of the control group at the end of the study by asking health care aides who work control facilities if they have ever encouraged residents in the control facilities to repeat sit-to-stands.

LTC facilities in the intervention group will be matched to the control group facilities on ownership model (public, private for-profit, voluntary not-for-profit) and size because quality of care and resident outcomes are associated with ownership models [49-54] and size [48,49,52]. To assess the comparability of the intervention and control facilities a research assistant will gather information about each facility by: a) interviewing managers to obtain information such as staff-to-resident ratios on each shift, availability of rehabilitation services and size of units; b) observing activity across both the day and evening shifts using a structured observation schedule; and c) measuring environments using two standardized instruments: the Alberta Context Tool and the Professional Environmental Assessment Protocol (PEAP). Drawing on data collected from the observations and data elicited during the manager interviews, total PEAP scores will be calculated immediately following each manager interview.

